### Hypotheses

#### Self-reported PTSI Symptoms and Resilience

The following 3 hypotheses were proposed:

H1: Symptoms of PTSI will be significantly reduced following the completion of the AMT intervention.H2: Functional wellness capacity and resilience will be significantly improved following the completion of the AMT intervention.H3: Sex and gender differences in PTSI will be observed at baseline and postintervention assessments.

Specifically, we expect that self-identified females will report more symptoms of PTSI and lower resilience at baseline, a greater reduction of PTSI symptoms, and a greater increase in resilience at follow-up than self-identified males. Gender role stress, discrimination, and harassment will be explored as moderators of PTSI symptoms at baseline and in response to the AMT intervention.

#### Objective Biological Indicators of PTSI Symptoms and Resilience

The following 4 hypotheses were proposed:

H4: Resting HRV will significantly increase following the completion of the AMT intervention.H5: RSA will significantly increase following the completion of the AMT intervention.H6: Recovery from acute stress will significantly improve following the completion of the AMT intervention.H7: Based on inconsistencies in the extant literature, we will conduct exploratory analyses of any potential sex and gender differences in HRV, RSA, and acute stress recovery at baseline and postintervention assessments.

## Methods

### Ethics Approval

This protocol has been approved by the University of Toronto’s Social Sciences, Humanities, and Education Research Ethics Board (Protocol #39478).

### Design

Capitalizing on the numerous long-standing professional relationships between study coinvestigators and police populations of interest, phase 1—development of the AMT intervention—will use an integrated knowledge translation (iKT) approach to generate user-informed content [42]. To test the effectiveness of the AMT intervention (phase 2), a cluster randomized control trial with parallel assignment will be used on several cohort samples of active-duty Canadian police officers. This study has been registered with ClinicalTrials.gov (NCT05521360).

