**Methods:**

The study is comprised of 2 phases. Phase 1 involves the development of the web-based AMT intervention, which includes 1 session of baseline survey measures, 6 weekly sessions that integrate HRV biofeedback (HRVBF) training with meta-cognitive skill practice, and 1 session of follow-up survey measures. Phase 2 will use a cluster randomized control design to test the effectiveness of AMT on the following prepost outcomes: (1) self-report symptoms of PTSI and other wellness measures; (2) physiological indicators of health and resilience including resting HR, HRV, and RSA; and (3) the influence of sex and gender on other outcomes. Participants will be recruited for an 8-week study across Canada in rolling cohorts.

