**Results:**

The study received grant funding in March 2020 and ethics approval in February 2021. Due to delays related to COVID-19, phase 1 was completed in December 2022, and phase 2 pilot testing began in February 2023. Cohorts of 10 participants in the experimental (AMT) and control (prepost assessment only) groups will continue until a total of 250 participants are tested. Data collection from all phases is expected to conclude in December 2025 but may be extended until the intended sample size is reached. Quantitative analyses of psychological and physiological data will be conducted in conjunction with expert coinvestigators.

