### Recruitment

We aim to test the AMT intervention on a sample of approximately 250 frontline police officers in rolling cohorts of 10-15 participants (half AMT, half waitlist control) from geographically representative police services across Canada. A power analysis was conducted using G*Power software [43] and found that a minimum total sample size of 128 participants was required (effect size f=0.25, α=.05, power=0.80, number of groups=2, number of repeated measures=2). However, we plan to oversample officers by sex and mitigate possible attrition based on the principal investigator’s previous experience with conducting longitudinal research on police officers [31-33]. A small laboratory-based prepilot sample (n=10) will test equipment reliability, accuracy, and integration of HR monitors with HRVBF and learning management system (LMS) platforms. An initial pilot cohort 1 (n=30) will then test the AMT intervention in the population of interest (ie, law enforcement officers) using a combined laboratory-remote paradigm to validate the implementation of study procedures. These participants will also be invited to participate in a poststudy focus group as per the study protocol (see iKT Focus Groups in Procedures) to optimize the intervention (ie, content and delivery) and overall study procedures to provide stakeholder- and user-informed feedback. When all user feedback has been incorporated, all subsequent participants will be tested fully remotely and in accordance with the randomized control trial procedures and group allocation.

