### Inclusion and Exclusion Criteria

Inclusion criteria included adults (aged 18 years or older) currently employed as active duty (ie, not retired or on an extended medical or disability leave) frontline law enforcement officers fluent in English. Exclusion criteria include non-Canadian law enforcement officers, police administrators, civilian employees (ie, nonsworn members), and officers that do not have regular access to a computer with internet access to complete the web-based AMT intervention. Scores on self-reported mental health screening tools completed during the preintervention sessions will be used to match the assignment of participants to experimental or control groups but will not be used to exclude participants based on established cutoff scores for high or severe PTSI symptoms.

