##### Session 1: Preintervention Assessment (1.5 Hours)

During this session participants will complete self-reported baseline measures of: (1) PTSI, including the Personal Health Questionnaire (PHQ-8) for major depressive disorder, General Anxiety Disorder Scale (GAD-7), Depression, Anxiety, and Stress Scale (DASS-42), PTSD checklist (PCL-5), Alcohol Use Disorder Identification Test (AUDIT), Perceived Stress Scale (PSS), and Personal Burnout Subscale of the Copenhagen Burnout Inventory (CBI) [65-71]; (2) resilience and well-being using the Brief Coping Orientation to Problems Experienced Inventory (Brief-COPE), Resilience Scale for Adults (RSA-33), Brief Resilience Scale (BRS), White Bear Suppression Inventory (WBSI), Perseverative Thinking Questionnaire (PTQ), Ultra Brief-Penn State Worry Questionnaire (UB-PSWQ), and Ultra Brief-Rumination Response Styles (UB-RRS) Questionnaire [72-78]; (3) functional wellness and occupational stress using the Sheehan Disability Scale (SDS), Good Health Practices Scale (GHPS), COVID-19 adapted version of the Holmes Rahe Stress Inventory (COVID-19 HRSI), World Health Organization Disability Assessment Scale (WHODAS 2.0) [79-82], operational and organizational subscales of the Police Stress Questionnaire (PSQ) [83], and Lam Employment Absence and Productivity Scale (LEAPS) [84]; and (4) sex and gender-relevant data using the Workplace Gender Discrimination Scale (WGDS) and Gender Experiences Questionnaire (GEQ) [85,86]. Global ratings of stress will be asked at the beginning of each AMT session using a sliding visual analog scale of 0 (not at all stressful) to 10 (extremely stressful) in response to 2 questions: “How stressful was this past week?” and “How stressed are you right now?.” Data will be immediately tabulated to randomly assign participants matched on demographic and outcome variables to either the experimental AMT intervention group that will continue with sessions 2-8 of the protocol or to the waitlist control group that will only be responsible for the first part of session 2 and all of session 8 (postintervention assessment).

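### The trial is labelled cluster randomised, but its procedures, its 128 and its ANCOVAs are those of individual randomisation within mixed cohorts; the unit must be stated once and cohort added to the models

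*Protocol article*

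**What the plan says.** **Label.** The Design section states that "a cluster randomized control trial with parallel assignment will be used on several cohort samples of active-duty Canadian police officers". The Abstract (Methods) repeats it: "Phase 2 will use a cluster randomized control design to test the effectiveness of AMT".

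**Allocation.** Under Session 1, the baseline data are used to "randomly assign participants matched on demographic and outcome variables to either the experimental AMT intervention group" or the waitlist control group. Inclusion and Exclusion Criteria says that screening scores "will be used to match the assignment of participants to experimental or control groups". Recruitment plans "rolling cohorts of 10-15 participants (half AMT, half waitlist control"). The Abstract (Results) is looser: "Cohorts of 10 participants in the experimental (AMT) and control (prepost assessment only) groups will continue until a total of 250 participants are tested".

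**Sample size.** Recruitment gives a minimum of 128 (f = 0.25, alpha 0.05, power 0.80, two groups, two repeated measures) and a target of about 250. The excess is attributed to oversampling by sex and to attrition.

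**Analysis.** Data Security and Analyses specifies repeated measures ANCOVAs, or ranked versions for non-normal self-report data, with sex, gender, age, years of service and geographic service region as covariates.

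**The concern.** A cohort that is half AMT and half control cannot itself be the allocated unit, and matching people on their own scores is a way of allocating people. So the label and the procedure cannot both be right. The choice matters because it fixes the valid error term. Under cluster allocation, the sample size needs a design effect and the model needs a cluster-level error. Under individual allocation within cohorts, neither is needed, but the cohort is a block and should be in the model. A reader who trusts the label must doubt the ANCOVA; a reader who trusts the procedure must conclude that the published design is misdescribed. This contradiction lies between statements the article makes, so it is not detail that was left to a fuller document.

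**Working it through.** **1. The allocated unit.**

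| Section | Unit implied |
|---|---|
| Abstract (Methods); Design | cluster, not named |
| Recruitment | both arms inside each cohort of 10 to 15 |
| Inclusion and Exclusion Criteria | participant, matched on own scores |
| Session 1 | participant, matched on own session 1 data |
| Abstract (Results) | ambiguous: 10 per arm, or 10 in all |

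The operative sections point to individuals.

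**2. Reproducing 128.** Take a two-group F test on independent individuals, with df 1 and N − 2 and noncentrality f²N. At N = 128 this is 0.0625 × 128 = 8, and the power is 0.80. So 128 reproduces exactly with no design effect. The listed inputs include no ICC or cluster size. (The listed two repeated measures do not lead to 128 at an assumed correlation of 0.5: the between-group form gives 98 and the interaction form 34. Neither form includes clustering.)

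**3. If individuals are allocated within cohorts.** With balanced arms in each cohort, cohort differences cancel from the treatment contrast. Its variance is (1 − ICC) times the variance that a model without cohort estimates.
- With cohort in the model, the equivalent of 128 is 128 × (1 − ICC), rounded up: 127, 122 and 116 at assumed ICCs of 0.01, 0.05 and 0.10.
- With cohort left out, the type I error is 2[1 − Φ(1.96/√(1 − ICC))]. At ICC 0.10 this is 2[1 − Φ(2.07)], about 0.04. The test is slightly conservative.

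**4. If whole cohorts are allocated.** The document gives no ICC, so the values are assumed. With m = 12.5, the midpoint of 10 to 15, DE = 1 + 11.5 × ICC. Power at the planned 250 is Φ(0.25√(250/DE) − 1.96), since f = 0.25 means a standardised difference of 0.5.

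| ICC | DE | Minimum 128 × DE, rounded up | Power at 250, no attrition |
|---|---|---|---|
| 0.02 | 1.23 | 158 | 0.95 |
| 0.05 | 1.575 | 202 | 0.88 |
| 0.10 | 2.15 | 276 | 0.77 |

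The noncentral F gives 0.94, 0.88 and 0.76. For m from 10 to 15, the minimum is 186 to 218 at ICC 0.05 and 244 to 308 at ICC 0.10. The ICC at which 250 just covers 128 is (250/128 − 1)/11.5 = 0.083 at m = 12.5.

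**5. Model terms.** Of the factors used in allocation, sex, gender, age and years of service are covariates, and each outcome's own baseline is the first repeated measure. Cohort is absent, as is any other screening score used for matching. Geographic region is a covariate but does not identify cohort or service.

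**The case against.** The best defence is that the document nearly settles the matter itself. Three operative sections describe individual assignment, no cluster is ever named, and the one loose sentence in the Abstract (Results) does not say that cohorts are allocated. On that reading 128 is right, the ANCOVA needs no cluster-level error, and what remains is a wrong word in two places plus a blocking term that a fuller document might supply. Most of this stands. It does not remove the contradiction, because the label appears in both the Abstract and the Design section, and the models list their covariates without cohort.

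A reader might infer more: that the trial is underpowered, or that the ANCOVA has an inflated type I error. By 2[1 − Φ(1.96/√DE)], the design effects above would give error rates of about 0.08, 0.12 and 0.18. The document does not support that inference, for three reasons.
- These figures require whole-cohort allocation, which the half-and-half cohorts contradict, and an ICC that nobody has stated.
- The planned sample is about 250, not 128, and before attrition it keeps power above 0.80 at two of the three assumed ICCs.
- The analysis is pre-post, so the relevant ICC is that of change, which may be smaller than that of a single measurement. The sessions are completed remotely, and no group sessions are described.

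A reader might also infer that the matching variables are missing from the model. Most of them are there.

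**Conclusion.** The point holds as an inconsistency: the design is called cluster randomised, while the allocation, the sample size and the models are those of an individually randomised trial with no cohort term. If allocation is individual, the consequence is a misdescribed design and a modest loss of precision (a factor of 1 − ICC in variance), with no inflation of type I error and no change to 128. The larger figures apply only if whole cohorts or services are allocated. They rest on assumed ICCs, 12.5 per cluster and no attrition; the document gives no attrition rate. Underpowering is not shown. The correction still matters, because the valid standard error depends on which statement is true.

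**What to change.** State the unit of randomisation once, and bring the Abstract (Methods and Results) and the Design section into line with Recruitment, Inclusion and Exclusion Criteria and Session 1.

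**If individuals are allocated**, as the procedures indicate:
- Replace the cluster label with 'individually randomised, matched within cohort'.
- Keep 128.
- Add cohort to every outcome model as a block term or random intercept. In a pre-post model the term must bear on change, for example follow-up adjusted for baseline with cohort in the model, since a constant cohort difference already cancels.
- Add any matching score that is not already a covariate or the outcome's own baseline.

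The cost is wording and a few degrees of freedom. At 250 participants there are about 17 cohorts (250/15) to 25 (250/10), so fixed blocks use 16 to 24, and a random intercept uses one variance parameter.

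**Only if whole cohorts or services are really allocated:**
- Name the cluster.
- Restate the minimum as 128 × [1 + (m − 1)ICC], with a stated and justified ICC.
- Use a mixed model with a random cluster intercept and small-sample degrees of freedom.

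The cost is a larger stated minimum, which may use up the margin now reserved for attrition and oversampling by sex.

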### Recruitment

We aim to test the AMT intervention on a sample of approximately 250 frontline police officers in rolling cohorts of 10-15 participants (half AMT, half waitlist control) from geographically representative police services across Canada. A power analysis was conducted using G*Power software [43] and found that a minimum total sample size of 128 participants was required (effect size f=0.25, α=.05, power=0.80, number of groups=2, number of repeated measures=2). However, we plan to oversample officers by sex and mitigate possible attrition based on the principal investigator’s previous experience with conducting longitudinal research on police officers [31-33]. A small laboratory-based prepilot sample (n=10) will test equipment reliability, accuracy, and integration of HR monitors with HRVBF and learning management system (LMS) platforms. An initial pilot cohort 1 (n=30) will then test the AMT intervention in the population of interest (ie, law enforcement officers) using a combined laboratory-remote paradigm to validate the implementation of study procedures. These participants will also be invited to participate in a poststudy focus group as per the study protocol (see iKT Focus Groups in Procedures) to optimize the intervention (ie, content and delivery) and overall study procedures to provide stakeholder- and user-informed feedback. When all user feedback has been incorporated, all subsequent participants will be tested fully remotely and in accordance with the randomized control trial procedures and group allocation.

Participants will be recruited in several ways: (1) partnering police services will provide a link to the web-based study hosted on the confidential University of Toronto (ie, not police-related) servers to members via email, announcements, and internal media postings with encouragement to participate; (2) the research team will visit police services and other related fora (eg, industry meetings and conferences) to hold recruitment and information days where eligible officers may sign up for the study; (3) our knowledge user (MLV) and expert police practitioner collaborator (PS) will facilitate recruitment of law enforcement officers through targeted media attention, networking, and professional outreach activities; (4) supporting stakeholder groups will facilitate communication and recruitment with users and law enforcement officers. Based on delays due to the COVID-19 pandemic, the order in which partner organizations are recruited and tested is subject to change based on availability and current public health guidelines.

Interested participants will be directed to a web-based consent form on a secure site that will detail the study aims, eligibility criteria, intervention protocol, allocation and procedures for experimental and control groups, risks and benefits, and other information related to their rights as a research participant (ie, confidentiality and contact information for PIs and the institutional ethics board). Participants will provide their informed consent by clicking on a link that will take them to an eligibility screening survey that will collect the following identifiable information: full name, mailing address (for equipment shipping and incentive payment), personal email address (for correspondence with the research team that is not monitored or accessible by the participants’ police agency), and demographics including sex at birth, gender, age, ethnicity, police service (to verify active duty status against publicly available directories), role, years of service as a police officer, and confirmation that they are not currently on extended medical leave. Participants deemed eligible for the study will be provided with deidentified usernames and passwords to access the preintervention assessment (see phase 2 procedures).

### Inclusion and Exclusion Criteria

Inclusion criteria included adults (aged 18 years or older) currently employed as active duty (ie, not retired or on an extended medical or disability leave) frontline law enforcement officers fluent in English. Exclusion criteria include non-Canadian law enforcement officers, police administrators, civilian employees (ie, nonsworn members), and officers that do not have regular access to a computer with internet access to complete the web-based AMT intervention. Scores on self-reported mental health screening tools completed during the preintervention sessions will be used to match the assignment of participants to experimental or control groups but will not be used to exclude participants based on established cutoff scores for high or severe PTSI symptoms.

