### Outcomes

In accordance with our hypotheses, PTSI (H1) will be measured by the PHQ-8, GAD-7, DASS-42, PCL-5, AUDIT, PSS, CBI, and self-reported stress visual analog scale. Self-reported resilience and well-being (H2) will be measured by the Brief COPE, RSA-33, BRS, WBSI, PTQ, UB-PSWQ, and UB-RRS. Functional wellness capacity and occupational stress will be measured by the SDS, GHPS, COVID-19 HRSI, WHODAS 2.0, PSQ, and LEAPS. Sex will be measured by self-reported sex at birth (male, female, or other); gender is measured by self-identification as male, female, nonbinary, or other (with the option to self-report) or “prefer not to disclose.” Sex and gender-related experiences will be measured by the WGDS and GEQ (H3 and H7). Changes in resting HRV (H4) will be measured by time and frequency domain parameters based on data collected from the wearable HR monitors (eg, high- and low-frequency HRV, low- or high- frequency ratio, and the Root Mean Square of Successive Differences, [RMSSD]) as recommended in the standards of practice for HRV analysis [17]. RSA (H5) will be measured by obtaining respiratory frequency. Greater power at the respiratory frequency indicates a higher level of RSA and will be analyzed using the gold standard HRV analysis program, Kubios [92]. Recovery from acute stress (H6) will be measured following completion of the web-based PASAT and emotional Stroop Tasks. Acute stress recovery will be assessed via a time-domain measure of HRV (RMSSD) [17].

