To test the effectiveness of the AMT intervention on improving biological indicators of resilience, prepost analyses of resting HRV parameters (H4), RSA (H5), and recovery from acute stress (H6) will be separately assessed using repeated measures ANCOVAs with sex, gender (H7), age, years of service, and geographic service region as covariates. To determine which factors significantly predict greater changes in biological outcome measures, hierarchical linear regression analyses will be undertaken with self-reported measures and demographic variables entered as predictors in the models. We will also compare weekly changes in HRV and RSA as measured during AMT module exercises with repeated measures ANCOVAs. A main effects analysis of the “time” variable will explore the potential incremental benefit of AMT training and identify at what point during the 6-week intervention significant biological changes occur. Computational approaches to analyzing and visualizing biological indices of resilience will be led by CM, including integration of cardiac (eg, HRV) and respiratory (eg, RSA) rhythms to elucidate patterns of desynchronization before, during, and following AMT.

To explore sex and gender-based contributions to self-report (H3) and objective indices (H7) of PTSI and resilience, the above analyses will include sex and gender as covariates or predictor variables with sex-stratified samples. These findings will clarify any sex-related differences in baseline and postintervention rates of PTSI and resilience among law enforcement officers and whether there are any sex-related differences in the magnitude of treatment effects (H3). Moderated regression analyses will test whether the AMT intervention affects the relationship between sex and PTSI symptoms and resilience. Multiple comparisons will be adjusted with Bonferroni corrections, where applicable.

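### No eligibility, screening, baseline or covariate item covers heart rhythm disorders, implanted devices or heart-rate-active or psychotropic medication, although H4-H6 rest on HRV

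*Protocol article*

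**What the plan says.** **Eligibility.** Under Inclusion and Exclusion Criteria, an eligible officer is an adult "currently employed as active duty (ie, not retired or on an extended medical or disability leave) frontline law enforcement officers fluent in English". The list of those kept out then opens: "Exclusion criteria include non-Canadian law enforcement officers, police administrators, civilian employees (ie, nonsworn members"). Lacking a regularly available internet-connected computer also rules an officer out. Mental health scores serve for matched allocation and "will not be used to exclude participants based on established cutoff scores for high or severe PTSI symptoms".

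**Screening.** Under Recruitment, the survey collects contact details and demographics, ending with "role, years of service as a police officer, and confirmation that they are not currently on extended medical leave". No heart condition or drug is named.

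**Baseline.** Session 1: Preintervention Assessment lists the battery instrument by instrument: symptoms, resilience, functioning, occupational stress, and sex- and gender-related experiences. None is described as covering cardiac history or medication.

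**Outcomes.** H4 is resting HRV in the time and frequency domains. H5 is spectral power at the breathing frequency. For H6, "Acute stress recovery will be assessed via a time-domain measure of HRV (RMSSD").

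**Analysis.** Under Data Security and Analyses, the H4-H6 models adjust for sex, gender, age, length of service and region. To find what predicts physiological change, "hierarchical linear regression analyses will be undertaken with self-reported measures and demographic variables entered as predictors in the models". The same section says that a coinvestigator will design cleaning procedures for the continuous physiological data. It does not give the rules.

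**The concern.** The article's own reason for measuring HRV (Biological Resilience: The Missing Piece) is that it reflects sympathetic and parasympathetic control of the heart. That reading fails in a fibrillating or paced rhythm, and drugs that act on heart rate or autonomic tone shift it. The article makes such participants plausible: its Background links posttraumatic stress injury to anxiety, depression and cardiovascular disease, and officers with severe symptoms stay eligible. After the pilot, testing is fully remote, with a chest-band monitor.

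Two things are at stake:

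- **Precision of the randomised H4-H6 contrasts.** Recordings that carry no autonomic signal widen the spread and dilute the effect.
- **Validity of the non-randomised analyses.** If officers with more symptoms more often take drugs that alter HRV, a symptom-to-HRV association can arise from the drug. If drug use differs by sex, the H7 comparisons are exposed in the same way.

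A later analysis plan can define covariates, but it cannot adjust for a variable that was never collected.

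**Working it through.** **1. Where could the information enter?**

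| Stage | Section | Health item named |
|---|---|---|
| Entry criteria | Inclusion and Exclusion Criteria | Not on extended medical or disability leave |
| Screening survey | Recruitment | Not on extended medical leave |
| Baseline battery | Session 1 | Symptom, resilience and functioning scales; no cardiac history or medication item |
| Model covariates | Data Security and Analyses | None |
| Regression predictors | Data Security and Analyses | Self-reported measures and demographics |

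The gap is the same at every stage.

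**2. The plan's own sample size, used as a yardstick.** Inputs from Recruitment: f=0.25, alpha 0.05, power 0.80, two groups, minimum N=128, planned N about 250. For a two-group F test with noncentrality λ = f²N and (1, N−2) degrees of freedom, N=128 gives λ = 0.0625 × 128 = 8.0 and power 0.8015, so 128 is reproduced. At N=250 the same test gives 0.976, before attrition and clustering. For two equal groups, f=0.25 is d=0.50.

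**3. Noise in the randomised contrast (assumed inputs).** The documents give no share of affected recordings. Suppose a share u shows no treatment effect and has s=3 times the SD. Then:

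- mean difference = 0.5(1−u)
- variance = (1−u) + u·s² + u(1−u)·0.25/2

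For u=5%, the difference is 0.475, the SD is √(0.95 + 0.45 + 0.0059) = 1.186, and d is 0.401.

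| Share u | d | Power, N=128 | Power, N=250 |
|---|---|---|---|
| 0 | 0.500 | 0.801 | 0.976 |
| 2% | 0.454 | 0.723 | 0.947 |
| 5% | 0.401 | 0.614 | 0.884 |
| 10% | 0.334 | 0.467 | 0.750 |

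With s=2 at N=250, power is 0.963, 0.936 and 0.872.

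A second illustration uses RMSSD. Assume a sinus-rhythm SD of 20 ms, an effect of 10 ms, and affected recordings 115 ms higher with SD 50 ms. The SD is √((1−p)·20² + p·50² + p(1−p)·115²). For p = 0.5%, 1% and 2% this gives 21.8, 23.5 and 26.5 ms, and d = 0.46, 0.43 and 0.38. Power is 0.73, 0.67 and 0.56 at N=128, and 0.95, 0.92 and 0.84 at N=250.

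**4. Leaving such recordings out instead.** From 250 enrolled, removing 2%, 5%, 10% or 20% leaves 245, 238, 225 or 200, with power 0.974, 0.970, 0.962 or 0.940. Discarding costs much less than keeping.

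**5. Confounding in the regressions (assumed inputs).** If symptoms and HRV are unrelated given the drug, the correlation induced by the drug is the product r(drug, symptoms) × r(drug, HRV). With 0.3 and −0.3 it is −0.09; with 0.5 and −0.5 it is −0.25; with 0.1 and −0.1 it is −0.01.

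**The case against.** **The cleaning step may remove bad recordings.** This stands. A reader might infer that unusable recordings will be analysed. The article does not support that: cleaning is planned, and its rules may sit in a fuller document. Cleaning need not recover the signal; it can reject the file. What remains is that, without cardiac history, some paced or irregular rhythms may be hard to recognise, and no cleaning of the signal reveals medication.

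**Randomisation protects the main contrast.** This stands too. A reader might infer that medication confounds H4-H6. Allocation is random and matched on demographic and outcome variables, so baseline medication adds noise or chance imbalance, not systematic bias. Drug changes during follow-up favour neither arm unless AMT causes them, and then they are part of its consequences.

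**The low power figures are worst cases.** Largely right. They rest on outside assumptions, and the lowest use the stated minimum of 128, not the planned 250. They also assume a comparison of post scores with nothing rejected. In the planned prepost analysis, a stable high level at both visits partly cancels. Likewise, stable medication matters less for change in HRV, the outcome of the predictor regressions, than for its level.

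**The printed lists may be incomplete.** The exclusions are introduced with a word that need not mean a full list, and a condensed article may omit a short health form. This weakens the point. But eligibility is core content that the article chose to set out, and neither the screening nor the baseline list names an item by which an unlisted criterion could be applied.

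**A broad population is deliberate.** Fair. This is a reason to keep these officers in the self-report analyses.

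**Conclusion.** The omission is real and consistent across eligibility, screening, baseline measurement and covariates. Its consequences are risks, not established faults:

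- **H4-H6:** possible added noise and some loss of power, depending on unstated cleaning rules. At the planned 250, before attrition and clustering, the assumed scenarios leave power between 0.750 and 0.963; only the most extreme (10% affected, three times the SD) falls below 0.80.
- **Symptom-to-HRV regressions and H7:** possible confounding by medication that could not be adjusted for. The assumed correlations give a spurious association from −0.01 to −0.25.
- **Randomised AMT versus control contrast:** no systematic bias.

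The document gives neither the frequency of rhythm disorders nor that of drug use, so the true size cannot be stated. This is a cheap improvement, not a flaw that undermines the trial.

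**What to change.** 1. Add two self-report items to the screening survey or to session 1, which precedes allocation: (a) known arrhythmia, pacemaker or other implanted rhythm device; (b) current heart-rate-active medication and current psychotropic medication, recorded as separate classes because their effects differ.
2. Prespecify, on baseline information alone and blind to arm, that participants positive on (a) are left out of the H4-H7 analyses and kept in H1-H3. A rule fixed this way does not disturb the randomised comparison.
3. Enter baseline medication as a covariate in the H4-H7 models and in the regressions of physiological change.
4. Record medication again at session 8, for description only. Do not drop participants who changed medication from the randomised comparison, because that conditions on a post-randomisation event. If such an analysis is run, label it exploratory.

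**Cost:** two extra questions, an ethics amendment, reliance on self-reported health data, and a few participants lost from the physiological analyses with slightly narrower generalisability. The Results section reports 7 registered pilot participants as of April 2023, so at that date the change could have preceded nearly all data collection.
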